## Abstract

**Methods::**

This study is a randomized, assessor-blind, parallel-group clinical trial. Eighty participants will be equally divided into experimental and control groups. Each participant will receive a total of 24 interventions over 12 weeks. The experimental group will receive EFT combined with acupuncture and the control group will receive acupuncture alone. The primary outcome is the change in the Beck Depression Inventory score from baseline to 12 weeks, and the secondary outcomes include change in the following variables: Beck Depression Inventory, Parkinson’s disease sleep scale, State-Trait Anxiety Inventory, the Korean version of the Fatigue, Resistance, Ambulation, Illnesses, and Loss of weight questionnaire scale, and unified Parkinson’s disease rating scale III and exercises.

**Discussion::**

Acupuncture is a safe and effective treatment for motor and nonmotor symptoms in PD, and EFT appears to be safe and effective for a variety of psychiatric symptoms. In this study, we will investigate the potential of EFT combined with acupuncture to improve psychiatric symptoms in PD.

## 1. Introduction

Parkinson’s disease (PD) is a widespread disease with its prevalence predicted to be 100 to 300 per 100,000 people.^[1]^ As the incidence of PD increases with age, the number of patients with PD is expected to increase significantly due to the general aging of the population.^[2]^ Therefore, the prevention, treatment, and management of PD are becoming increasingly important. Approximately 35% of patients with PD have depression, and their activities of daily living and cognitive function decrease faster than those without depression.^[3,4]^

Acupuncture is a clinically effective and safe treatment for motor and nonmotor symptoms such as psychiatric disorders, sleep problems, and gastrointestinal symptoms in patients with PD.^[5,6]^

The emotional freedom technique (EFT) is a type of psychological therapy that assesses targeted psychological issues.^[7]^ It alleviates psychological problems by stimulating acupoints without acupuncture.^[8]^ The EFT has been proven to effectively improve depression, anger, and anxiety in a variety of populations^[8–10]^ and improve a variety of diseases such as sleep disorders, constipation, allergies, and blood pressure.^[7]^

In South Korea, the increase in social and health care costs due to PD is emerging as an important social problem.^[11,12]^ Therefore, the demand for drugs or health technologies that treat the psychiatric symptoms of PD is continuously increasing.

The main pathogenesis of PD is the degeneration of the dopaminergic area, which results in not only motor symptoms such as bradykinesia and resting tremors, but also psychiatric symptoms such as dementia, cognitive decline, depression, and sleep disorders.^[13]^ In addition, motor disability in PD can lead to severe negative social consequences and easily result in depression.^[14]^ These psychiatric symptoms affect the quality of life of patients and caregivers.^[15]^ Therefore, various approaches, including continuous management and treatment, are required for PD against accompanying nonmotor symptoms.^[16]^ Since the psychiatric symptoms of PD are closely related to changes in motor and nonmotor symptoms, the main conventional treatment for PD is dopamine supplementation, and anti-depressants can be used to alleviate depression and anxiety symptoms.^[17]^ However, dopamine supplementation may worsen the psychiatric symptoms of PD and anti-depressants may be related to the deterioration of motor symptoms.^[15]^ Therefore, studies about safer complementary non-pharmacological treatment options are required.

In this study, we will compare the efficacy, safety, and economic efficiency of EFT combined with acupuncture and acupuncture alone for the psychiatric symptoms of PD.

## 2. Methods/design

### 2.1. Study design

This study is a randomized, assessor-blind, parallel-group clinical trial. This clinical trial will be conducted at Daejeon Korean Medicine Hospital of Daejeon University. This protocol (version 1.6, February 2022) complies with the Recommendations for Interventional Trials (SPIRIT) Standard Protocol guidelines. All items from the World Health Organization Trial Registration Data set are described in Table S1, Supplemental Digital Content, http://links.lww.com/MD/I936.

### 2.2. Study procedure

Before conducting this clinical trial, the investigator will explain the “Informed consent form” to the participants and receive written consent from the participants for the clinical trial based on their free will after ensuring that they have sufficiently understood what is required of them. The subjects will be given a screening code after obtaining their consent.

# DJ-S-ZZZ [DJ: Daejeon Korean Medicine Hospital of Daejeon University, S: initial screening, ZZZ: Serial number (001, 002–)] (ex. DJ-S-012: 12th applicant for screening of Daejeon Korean Medicine Hospital of Daejeon University).

The eligible subjects who meet the inclusion and exclusion criteria will be selected based on a demographic information survey, vital signs (blood pressure, pulse rate, and body temperature), physical examination, medical history (including chief complaint, onset, motif, past history, smoking, and alcohol ingestion), Hoehn & Yahr scale, 15-item geriatric depression scale (GDS-15), Korean Mini-Mental State Examination (MMSE-K), chest X-ray, electrocardiography (EKG), and laboratory tests at screening. The included subjects will be assigned an identification code.

Check concomitant drugs		●	●	●	●	●	●
Check Adverse effects			●	●	●	●	●
Acupuncture		●	●	●	●	●	
EFT		●	◎	◎	◎	◎	
BDI		●		●		●	●
PDSS		●		●		●	●
STAI		●		●		●	●
K-FRAIL		●		●		●	●
UPDRS Ⅲ		●		●		●	●
fNIRS		●				●	
Efficacy assessment		●		●		●	●
Cost analysis		●		●		●	●
Exercise measurements		●		●		●	●
Compliance measurements			●	●	●	●	
Education of visit schedule		●	●	●	●	●	

### 2.3. Clinical assessments

In this study, the clinical assessments are as follows: vital signs (blood pressure, pulse rate, and body temperature); laboratory tests (complete blood cell count: hemoglobin, hematocrit, red blood cell count, white blood cell count, platelet count, erythrocyte sedimentation rate; blood chemistry test: total protein, albumin, aspartate transaminase, alanine transaminase, gamma-glutamyl transpeptidase, total bilirubin, blood urea nitrogen, creatinine, glucose, Na+, K+, Cl−, free thyroxine, thyroid-stimulating hormone; urine analysis: specific gravity, pH, erythrocyte, leukocyte, nitrite, protein, glucose, ketone, urobilinogen, bilirubin, microscopy); pregnancy test (urine human chorionic gonadotropin, only for fertile women, to ensure that the results are negative); EKG (12 leads electrocardiography); chest X-ray; GDS-15; Hoehn & Yahr Scale; BDI-II; PDSS; STAI; K-FRAIL; UPDRS III; EQ-5D; EQ-VAS; cost analysis; MMSE-K.

### 2.4. Study populations

#### 2.4.1. Inclusion criteria.

Aged 45 to 85 yearsDiagnosed with PDHoehn and Yahr Scale score of 1 to 3The 15-item Geriatric Depression Scale (GDS-15) score of over 6MMSE-K score of over 24Participants who voluntarily decided to participate and signed the consent form

#### 2.4.2. Exclusion criteria.

Patients with dementia, Huntington’s disease, or hydrocephalusPatients with gait disturbance due to cerebral vascular accidents, brain tumors, or other cerebral diseasesParticipants who have taken or changed the dosage of antiparkinson medication, materials, or medications that may affect depression (e.g., anti-anxiolytic drugs, anti-depressive drugs, anti-psychotic drugs, steroids, female hormones, L-dopa, digitalis, bromide, cyclosporin, disulfiram, isoniazid, yohimbine), in the previous 2 weeksPatients who cannot participate in the trial due to lab test results (e.g., over 2 times the upper reference limit of aspartate transaminase, alanine transaminase, total bilirubin, or creatinine)Seriously unstable medical conditions (the investigator will decide based on vital signs, EKG, and chest radiograph by the standard operating procedure. E.g., active tuberculosis on chest radiograph or signs of ventricular fibrillation or myocardial infarctions on EKG)Participants who have been treated with Korean medical treatment related to PD in the past 2 weeks, since that treatment may affect this trial or its safety.Pregnant or lactating womenParticipants who are thought to be not appropriate to participate in this trial by the investigator.

#### 2.4.3. Sample size.

The statistical hypothesis test of the evaluation variable is two-sided and the significance level will be set at 5%. The type 2 error(β) will be set to 0.2, and the power will be maintained at 80%. The ratio of the experimental and control groups should be 1:1. We expect the BDI reduction and standard deviation of the acupuncture group to be 2.8 and 7.8, respectively, and the BDI reduction of the experimental group to be 7.8, based on previous studies conducted with a design similar to this study.^[18,19]^ Therefore, the required sample size for each group is expected to be “2*6.92(1.96 + 0.84)2/(7.8 − 2.8)2 ≃ 30/group.” In addition, considering the dropout rate of 25%, we have decided to register 40 participants per group, with a total of 80 participants.

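### The sample size text gives an SD of 7.8, but the formula reaches 30 per group only with about 6.9, so 80% power does not follow from the stated inputs

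*Protocol article*

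**What the plan says.** All of the inputs are in section 2.4.3 of the protocol article.

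- **Test and error rates:** "The statistical hypothesis test of the evaluation variable is two-sided and the significance level will be set at 5" per cent, and "The type 2 error(β) will be set to 0.2, and the power will be maintained at 80" per cent.
- **Allocation:** "The ratio of the experimental and control groups should be 1:1".
- **Acupuncture group:** "We expect the BDI reduction and standard deviation of the acupuncture group to be 2.8 and 7.8, respectively".
- **Experimental group:** "the BDI reduction of the experimental group to be 7.8". No SD is given for this arm, and no pooled SD is mentioned.
- **Result:** presented as following from these inputs, "2*6.92(1.96 + 0.84)2/(7.8 − 2.8)2 ≃ 30/group". A dropout rate of 25% then takes this to 40 per group, 80 in total.

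The inputs are attributed to two cited earlier studies. Section 2.11.1 names an independent t test on the change in BDI from baseline to 12 weeks as the primary comparison.

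**The concern.** The sentence and the formula should use the same SD, and they do not. The only SD in the text is 7.8, yet the variance term in the formula starts from 6.9 ("2*6.92(1.96 + 0.84)2", where the trailing 2s are squares that lost their superscript). The figure 7.8 is also the expected reduction in the experimental arm, so a copying slip is possible in that sentence.

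This calculation is the only justification in the article for the number of patients. As written, a reader cannot tell whether 30 evaluable patients per arm give roughly the intended power for a 5-point difference, or about 10 percentage points less.

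**Working it through.** **Inputs (section 2.4.3):** two-sided 5% (1.96), power 80% (0.84), 1:1 allocation, difference δ = 7.8 − 2.8 = 5.0, dropout 25%. Equal SDs in both arms are assumed unless stated otherwise.

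**Formula:** n per group = 2 × SD² × (1.96 + 0.84)² / δ².

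**Step 1: reproduce the plan's figure.**
- SD 6.9: 2 × 47.61 × 7.84 / 25 = 29.86, so 30. Then 30 / 0.75 = 40 per group. This matches the article.
- Reading the printed digits as 6.92 squared: 30.03, again about 30.
- Reading them as an unsquared 6.92: 4.34, which does not match.

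**Step 2: use the SD in the text.**
- SD 7.8: 2 × 60.84 × 7.84 / 25 = 38.16, so 39. Then 39 / 0.75 = 52 per group, 104 in total, against 80 planned.
- With the t distribution in place of the normal, 40 evaluable per group are needed; 40 / 0.75 = 53.3, so 54 per group, 108 in total.
- A one-sided test with SD 7.8 would need 31 per group. That is close to 30, but the text says two-sided and the formula uses 1.96, so it does not explain the figure.

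**Step 3: power at the planned numbers.** Normal approximation: power = Φ(δ / (SD × √(2/n)) − 1.96). The t-test figures use the noncentral t distribution with 2n − 2 degrees of freedom.

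| Common SD | Evaluable per arm | δ / (SD × √(2/n)) | Normal approximation | t test |
|---|---|---|---|---|
| 6.9 | 30 | 2.81 | 80.1% | 78.8% |
| 7.8 | 30 | 2.48 | 69.9% | 68.5% |
| 7.8 | 40 | 2.87 | 81.8% | 80.8% |

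With SD 7.8 and 30 per arm, the difference detectable with 80% power by the t test is 5.74 points.

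**Step 4: could both figures be right?** If 6.9 is a pooled SD for two equal groups and 7.8 belongs to the control arm, the experimental-arm SD would be √(2 × 6.9² − 7.8²) = √(95.22 − 60.84) = √34.38 = 5.86, about 5.9. That is arithmetically possible, but neither this value nor any pooling step is in the article.

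**The case against.** A reader might infer that the trial is underpowered, at 68% instead of 80%. The documents do not support that as a fact. It holds only if 7.8 is the common SD, and two other readings remain open.

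- **Copying slip.** The SD may have been meant as 6.9 and overwritten by the 7.8 of the experimental arm. The step from 30 to 40 per group is then sound, and only one figure in the sentence is wrong.
- **Unstated pooling.** The 7.8 is attached to the acupuncture group alone, and two source studies are cited. A pooled 6.9 would leave both figures correct and power near plan. The article condenses a fuller protocol that may contain the step.

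Both readings stand as possibilities, and neither removes the point. On each, the printed passage is incomplete or wrong: an SD is misstated, or the SD that was actually used is missing. Lost superscripts explain the trailing 2s but cannot turn 7.8 into 6.9.

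It can also be said that 30 per arm is the number left after the full 25% loss, whereas section 2.10 makes the full analysis set, with imputation, primary. That is fair: 68.5% is the figure at the planned loss, not a fixed property of the trial. But 30 is the number for which the article claims 80%, and imputation does not restore the information lost. Even with no loss at all, SD 7.8 gives about 81%.

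A reader might also infer that baseline adjustment would make good any shortfall. The gain depends on the correlation between baseline and week 12, which the article does not give, and section 2.11.1 plans a t test, with covariance analysis only if baselines differ.

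**Conclusion.** The inconsistency is established: the figure of 30 per group rests on an SD of about 6.9, while the only SD stated is 7.8, which gives 39 per group by the same formula. The 80% power therefore does not follow from the inputs as written.

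The consequence for power is conditional. For a difference of 5.0, a two-sided 5% test, equal SDs and 30 evaluable per arm, power is about 68–70% if the common SD is 7.8 and about 79–80% if it is 6.9. If 7.8 is right, 80% is reached only when practically all 40 per arm contribute, which uses up the dropout allowance. Which SD is right cannot be decided from the article; it needs the two cited sources or the full protocol.

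**What to change.** Check the source studies, then state in section 2.4.3 which SD is meant, where it comes from and whether it is pooled, so that sentence and formula agree.

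- **If 6.9 is the common SD:** correct the sentence. Sample size and formula stand.
- **If 6.9 is pooled:** state the SD of each arm (with 7.8 in the control arm, about 5.9 in the experimental arm) and the pooling step. The 7.8 should then not be replaced.
- **If 7.8 is the common SD:** correct the formula, keep N = 80, and restate the operating characteristics for the planned t test: about 68% power at 30 evaluable per arm, about 81% only if all 40 per arm contribute, and a detectable difference of about 5.7 points at 30 per arm.

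The cost is a change of wording in section 2.4.3, with no extra patients and no change to the analysis. The only downside is that the stated power may become less favourable.

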#### 2.4.4. Randomization, blinding.

The people in charge of other assignments (or independent statisticians), who are not involved in conducting and evaluating this clinical trial, will generate a random assignment list in a specific and reproducible manner. A block randomization method will be used for randomized allocation. The random assignment table will be kept sealed and managed separately by the research manager in the presence of the participants. Each group will be randomly assigned with the chance of each individual being selected using the statistical program SAS® version 9.4 (SAS Institute. Inc., Cary, NC). The investigators and assessors will be separated so that the investigators will not know what kind of treatment the subjects have received. It is not possible to maintain investigator blindness.

### 2.5. Interventions

The EFT combined with the acupuncture group (experimental group) will receive EFT once a week for 12 weeks (a total of 12 times) and acupuncture treatment twice a week for 12 weeks (a total of 24 times). In the experimental group, acupuncture will be performed after the EFT. Acupuncture treatment will be performed on a total of 15 acupoints: GV20, GV24, EX-HN3, as well as bilaterally at LI11, PC6, HT7, ST36, SP6, and KI3” for better clarity. The acupuncture alone group (control group) will receive acupuncture treatment twice a week for 12 weeks (a total of 24 times). Acupuncture treatment will be the same in both the experimental and control groups. The STRICTA results of acupuncture treatment are described in Table 2.

**Table 2 T2:** STRICTA of acupuncture treatment.

STRICTA list		Description
1)Acupuncture rationale	a) Style of acupuncture	Meridian of Traditional Korean Medicine
	b, c) Reasoning for treatment provided, based on historical context, literature sources, and/or consensus methods, with reference where appropriate	Textbook of the meridian, Korean medical clinical practice guidelines for Parkinson’s disease, depression, literature review of acupuncture for Parkinson and depression.
2)Needling details	a) Names (or location if no standard name)	GV20, GV24, EX-HN3, LI11, PC6, HT7, ST36, SP6, KI3
	b) Number of needle insertions per subject per session	15
	c) Depth of insertions, based on a specified unit of measurement, or on a particular tissue level	Vertical insertion, 5–30 mm
	d) Response sought	None
	e) Needle stimulation	Manual
	f) Needle retention time	30 min
	g) Needle type	0.25 mm × 30 mm, Dongbang medical, stainless steel
3)Treatment regimen	a) Number of treatment sessions	24
	b) Frequency and duration of treatment sessions	twice a week for 12 weeks (24 times in total)
4)Co-intervention	a) Details of other interventions administered to the acupuncture group	Emotional Freedom Technique (EFT) (only in the experimental group)
5)Practitioner background	a) Description of participating acupuncturists	a specialist of neuropsychiatry or internal medicine of traditional Korean medicine, or a resident who is being educated by the specialist of neuropsychiatry or internal medicine of traditional Korean medicine, and have clinical experience in neuropsychiatry or internal medicine of traditional Korean medicine for over 1 year.
	b) Years in acupuncture practice	over 1 year.
	c) Qualification or professional affiliation	a specialist of neuropsychiatry or internal medicine of traditional Korean medicine, or a resident who is being educated by the specialist of neuropsychiatry or internal medicine of traditional Korean medicine, and has clinical experience for over 1 year.

EFT will be performed by a specialist in neuropsychiatry or internal medicine of traditional Korean medicine, or a resident who has been educated by a specialist in neuropsychiatry or internal medicine of traditional Korean medicine and has clinical experience in neuropsychiatry or internal medicine of traditional Korean medicine for over 1 year.

We will follow the EFT protocol suggested in the EFT manual (2008).^[20]^ It consists of 6 stages: goal setting and confirming the problem, setup, sequence, the 9 Gamut sequence, sequence, and EFT reframing. We modified the protocol and constructed it in 6 stages as described in Table 3.

**Table 3 T3:** EFT protocol.

1)Goal setting and symptom identification	Decide a psychological or somatic symptom to resolve, and score present distress between 0 to 10.
2)Preparation	Repeat the following words while tapping or massaging the points on the hands and chest. (“Even though I feel uncomfortable about my ___, I deeply and completely accept myself.”)
3)Basic tapping	While repeating simple words that can remind the uncomfortable situations, tap each meridian point 7 times.
4)Brain tuning	While tapping TE3, close and open the eyes, and then move the pupils towards the lower right side, lower left side, turn clockwise, and then counterclockwise. Sing a single line of a simple song and count the number (1–5).
5)Basic tapping	Repeat 3) Basic tapping
6)Reevaluation and additional tapping	Reevaluate the present distress. If it was not changed at all, identify other issues or distress by 1) step. If it was slightly reduced, repeat 2) -5).

### 2.6. Criteria for concomitant drugs

#### 2.6.1. Possible drugs.

If doses of antiparkinson drugs and psychiatric drugs (e.g., anti-depressants, anti-anxiety medication, tranquilizers, and sleeping pills) are consistent for 4 weeks before participating in the trial, it is permissible. Drugs for transient care of other diseases will be medicated after confirmation by the researcher. When concomitant drugs, including drugs for other diseases or adverse events, are administered, information about the drugs, including name, purpose, dose, and duration, will be recorded in a progress note.

#### 2.6.2. Prohibited drugs.

There are no specific combination-prohibited drugs, but the drugs that can affect results can be prohibited depending on the decision of researchers (e.g., starting with new medications, such as anti-depressants, anti-anxiety drugs, tranquilizers, corticosteroids, female hormones, L-dopa, digitalis, bromide, cyclosporin, disulfiram, isoniazid, and yohimbine, during the clinical trial.).

### 2.7. Adverse event report

The investigator will report any severe adverse events to the principal investigator (PI) regardless of whether they are related to the intervention during the trial. In addition, events associated with the intervention that are considered by the investigator to be of significant danger will be recorded in the progress note as severe adverse events. In this study, the following are considered as severe adverse events: death; life-threatening events; the need for hospital admission or to extend the admission period; events resulting in continuous or severe disability or impairment of function; events requiring treatment due to other critical medical situations.

When severe adverse events occur, the PI will notify the client (Daejeon Korean Medicine Hospital of Daejeon University) immediately and provide an additional report, including details, within 5 days. The trial should be stopped until further instructions are provided. The client should promptly report any severe or unexpected adverse events to other relevant investigators, the Institutional Review Board (IRB), and the Director of the Ministry of Food and Drug Safety.

### 2.8. Criteria for discontinuation or dropout

#### 2.8.1. Discontinuation.

In the case of an adverse event that can have an adverse effect on the safety of participants or can affect the clinical trial, the ongoing test should be discontinued, excluding the safety assessment. The PI and the client will discuss the safety of the intervention and decide whether to proceed with or discontinue the trial.

